## Abstract

**Background:**

Insufficient migration and activation of tumor specific effector T cells in the tumor is one of the main reasons for inadequate host anti-tumor immune response. External radiation seems to induce inflammation and activate the immune response. This phase I/II clinical trial aims to evaluate whether low dose single fraction radiotherapy can improve T cell associated antitumor immune response in patients with colorectal liver metastases.

**Methods/Design:**

This is an investigator-initiated, prospective randomised, 4-armed, controlled Phase I/II trial. Patients undergoing elective hepatic resection due to colorectal cancer liver metastasis will be enrolled in the study. Patients will receive 0 Gy, 0.5 Gy, 2 Gy or 5 Gy radiation targeted to their liver metastasis. Radiation will be applied by external beam radiotherapy using a 6 MV linear accelerator (Linac) with intensity modulated radiotherapy (IMRT) technique two days prior to surgical resection. All patients admitted to the Department of General-, Visceral-, and Transplantion Surgery, University of Heidelberg for elective hepatic resection are consecutively screened for eligibility into this trial, and written informed consent is obtained before inclusion. The primary objective is to assess the effect of active local external beam radiation dose on, tumor infiltrating T cells as a surrogate parameter for antitumor activity. Secondary objectives include radiogenic treatment toxicity, postoperative morbidity and mortality, local tumor control and recurrence patterns, survival and quality of life. Furthermore, frequencies of systemic tumor reactive T cells in blood and bone marrow will be correlated with clinical outcome.

**Discussion:**

This is a randomized controlled patient blinded trial to assess the safety and efficiency of low dose radiotherapy on metastasis infiltrating T cells and thus potentially enhance the antitumor immune response.

**Trial registration:**

ClinicalTrials.gov: NCT01191632

## Background

Colorectal cancer (CRC) is the most frequent cancer in the western world [1]. Advanced tumor stage with metastasis is one of the main reasons for the high mortality rate. At the time of diagnosis, approximately 30% of patients have distant metastases which predominantly occur in the liver. Surgical removal of the tumor still remains the only curative approach [2,3]. In recent years survival rates in colorectal cancer have been further improved because of multimodal therapy concepts, especially in UICC stage III and IV patients. In parallel to these modern multimodal therapy concepts, novel and promising concepts including immunotherapeutic strategies are actively being investigated to further improve clinical outcome.

Most patients with CRC have high numbers of tumor specific T cells (cytotoxic T cells and T helper cells) in their blood and bone marrow [4,5]. The molecular identification of tumor-associated antigens (TAA) has led to the development of antigen-specific immunotherapy targeting these antigens. To the present these strategies have failed to show efficacy in clinical practice. Potential reasons for this lack of efficacy include the inefficiency of T cell activation in vivo, insufficient migration of cytotoxic T cells into the tumor, the choice of irrelevant antigens, induction or application of monovalent T cells or the treatment of patients in highly advanced tumor stages [6]. In particular inadequate T cell infiltration, characterized by selective recruitment of immune suppressive regulatory T cells as well as insufficient immigration of cytotoxic T cells [7-9] appears to be a serious hurdle, partially explainable by poorly activated endothelium of the tumor vessels [10]. Furthermore, the cytotoxic and secretory activity of tumor specific T cells may be inhibited by the immunosuppressive environment of the tumor stroma after immigration into the tumor.

Ionizing radiation therapy (RT) is an effective local cancer therapy, which kills cancer and other cells within the tumor stroma, including endothelial cells and intratumoral lymphocytes [11]. RT typically induces primarily mitotic cell death but also leads to apoptosis [12]. Radiation has also complex effects on the tumor microenvironment and microvessels, which can facilitate the homing of both antigen presenting and effector T cells to the tumor [10,13].

Tumor cells killed by RT may be a good source of antigens for Dendritic Cell (DC) uptake and presentation to T cells. DCs are attracted by the altered microenvironment and undergo maturation after internalizing the debris. These dendritic cells can then present tumor specific antigens to T-cells following the processing of debris [14]. The possibility of using RT to promote tumor antigen-presentation by DC has been explored. Sublethal doses of ionising radiation have been described to enhance antitumor T-cell activity in such indirect ways in animal studies. Radiation has also been described to directly lead to an amplification of expression of MHC. This can render tumor cells more sensitive to the detection and lysis by specific T-cells [15]. Furthermore ionizing radiation can lead to activated endothelium thus facilitating the immigration of T-cells into the tumor. Overall, the available preclinical in vivo data support the hypothesis that RT may provide at least some of the necessary maturation signals.

So far, no systematic clinical analysis has been performed to investigate the immune stimulatory effects of low dose radiotherapy in patients with CRC. One issue to be addressed is the effective radiation dose to act as a form of immunotherapy. In fact, scant data are available with regard to the specific radiosensitivity of the different cellular components of the immune system. Studies describing the effects of RT on circulating immune cells are also lacking along with data on radiation effects on the microenvironment.

We here present the protocol of a clinical phase I/II trial with the aim to determine the active local external beam radiation dose resulting in tumor infiltrating T cells in patients with liver metastasis from CRC. The liver metastases will be irradiated two days prior to surgery using external beam radiotherapy. As primary endpoints we will determine the active local radiation dose leading to metastasis infiltrating T cells as a surrogate parameter for antitumor activity. Secondary objectives include local tumor control, survival, treatment toxicity as well as quality of life. Furthermore, blood cell transcriptomics and plasma-proteomics will be correlated with the amount of tumor reactive T cells in blood and bone marrow.

## Methods/Design

### Trial population and patient recruitment

This trial focuses on patients with resectable liver metastases of CRC. Patients scheduled for elective hepatic resection due to colorectal liver metastasis will be enrolled in this study. Only patients over 50 years of age are allowed to participate in this study due to the radiation protection law. Based on the preoperative imaging the surgeon determines if the liver metastasis can be resected in curative intent. Patients with unresectable liver metastasis, secondary malignancies, liver cirrhosis or previous radiotherapy to the upper abdomen will be excluded from the trial (see Table 1).

**Table 1 T1:** Eligibility criteria

Inclusion criteria
Liver metastasis of colorectal cancer
Metastasis is curatively resectable
Written informed consent of the patient
No evidence of active or former concurrent malignant diseases

**Exclusion criteria**

Previous radiotherapy to the upper abdomen
Participation in other therapeutical trials
Liver cirrhosis
Pregnancy
No willingness on regular follow up care
Any extrahepatic disease

Patients who meet the eligibility criteria and provide written informed consent are randomly allocated to either study intervention to balance treatment groups for all known and unknown potentially confounding factors. A block randomisation list is created via a computer system. Patients are randomised using consecutively numbered opaque envelopes prepared and sealed by an independent study nurse. The envelopes will be opened sequentially only after the participant's name is written on the appropriate envelope. Neither the screening investigators nor the investigators who inform the potential participants about this trial and enrolling the patients, have any knowledge of the block randomisation list or the previous allocations to treatment. There is no stratification for randomisation.

After informed consent, patients are randomized either to the control group - receiving no radiation - or the three irradiation treatment groups. Within the irradiation treatment groups patients will receive 0.5 Gy, 2 Gy or 5 Gy single fraction radiation 48 h prior to resection. After the adjustment of an individual positioning device, computed tomography and, if needed, magnetic resonance imaging (MRI) treatment planning examinations are performed. After 3D inverse treatment planning and plan optimizing using VIRTUOS and KONRAD software, intensity modulated radiation therapy will be administered using five to nine 6 MV linear acceleration (LINAC) photon beams. Immediately prior to the irradiation the setup error of the patient will be determined via In-Room-CT, and corrected if necessary.

The first blood sample will be obtained (54 ml) before radiation, a second just prior to the start of the operation. A bilateral bone marrow sample (27 ml each) will be taken from both iliac crests after induction of general anaesthesia just before skin incision. Bone marrow sampling is optional for the patient. EDTA will be used as anticoagulant for bone marrow and blood samples. After hepatic resection a part of the tumor will be immediately removed and stored at -80°C for further analyses.

On the postoperative day seven and at the follow-up/restaging visits (4 weeks postoperatively, four and seven months postoperatively) additional venous blood samples (54 ml) will be obtained. Quality of Life will be tested using the EORTC QLQ C-30 at four months and seven months postoperatively. Clinical examination will be performed and blood samples will be obtained by the investigators at all visits.

Curative surgery requires complete resection of all liver metastases, regardless of size, number, distribution, or width of resection margin. Liver operation will be carried out under low central venous pressure using a Péan clamp, ultrasonic dissector or vascular stapler. An intraoperative ultrasound of the liver will be performed in all patients to assess the relationship of the lesions to major vessels and to rule out additional lesions. The Brisbane 2000 terminology of hepatic anatomy and resections will be applied [16].

### Safety aspects and adverse events

As the radiation dose is relatively low, very few side effects are expected. Potential adverse events (AE) include skin alterations like redness, temporary elevated transaminases, transient nausea or diarrhea. All possible AEs will be assessed by the RTOG Scale. These AEs rarely occur in conventional radiotherapy using considerably higher doses (neoadjuvant 5 × 5 Gy for rectal or gastric cancer, 54 Gy in pancreatic cancer) [17,18].

### Study design

This single fraction radiation on colorectal liver metastases trial is a registered (ClinicalTrials.gov - NCT01191632), investigator-initiated, prospective, randomized controlled phase I/II trial to evaluate the optimal neoadjuvant, single fraction radiation dose for patients undergoing resection for colorectal liver metastases in curative intent. Patients will be randomised either to the control group -receiving no radiation- or the three treatment groups - receiving 0.5 Gy, 2 Gy or 5 Gy single fraction radiation to the metastasis 48 h prior to the operation. The treatment is offered to a heterogeneous group of patient of both sexes, covering a wide range of comorbidities. For the irradiation a highly conformal dose distribution to the tumor with 1 cm safety margin is delivered using a 6 MV LINAC and intensity modulated radiotherapy (IMRT) treatment application. After inclusion of 20 patients an interims analysis will be performed. The final analysis will be performed within three month of the inclusion of the last patient. The trial design will not be changed without prior agreement of the ethics committee.

Translational studies will be carried out by the Department of Translational Immunology of dkfz, the Radiation Oncology Departments of German Cancer Research Center (DKFZ) and the Surgery Departments of the University Hospital. This trial is an investigator-initiated trial and is coordinated by the Department of General-, Visceral- and Transplantation Surgery and the Radiation Oncology Department of DKFZ. The Radiation Oncology Department of DKFZ is responsible for the overall trial management, trial registration, database management, quality assurance including monitoring and scientific program of all trial related meetings. The methods and the study design of this trial have the same structure as the previously published study protocol for patients with pancreatic cancer (BMC Cancer 2011; 11:34) [19].

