### Objective of the study

The primary objective of this trial is the determination of the single fraction radiation dose, measured by the number of tumor infiltrating T-cells in the tumor. Secondary molecular objectives are the T cell activity in the resected tumor specimen, the density of regulatory T cells, and the frequency of tumor reactive T cells in blood and bone marrow in correlation with changes in the level of proteins involved in immune response or angiogenesis and transcriptomics in whole blood cells. Further clinical secondary objectives are acute radiogenic toxicity, postoperative morbidity and mortality, local control, recurrence patterns, overall survival and quality of life. All clinical secondary objectives are presented in Table 2.

**Table 2 T2:** Secondary endpoints

Secondary endpoints
• Local control and recurrence patterns of colorectal liver metastasis • Progression free survival • Surgical morbidity in patients undergoing liver resection who received this protocol treatment • 30 day postoperative mortality • Radiation toxicity • Quality of life according to EORTC QoL questionnaire after 3 and 6 months

Currently, 35 patients are randomized. The duration of the trial is expected to last four more months. Usually, two patients per month can be enrolled into this study. Evaluation and reporting of the clinical and laboratory results will be done within three months after the end of recruitment and closing of the database.

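### The final analysis is timed before the last patients' four- and seven-month visits, and nothing limits it to the primary tissue endpoint

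*Protocol article*

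**What the plan says.** **Timing of the analysis.** Protocol article, Study design: "The final analysis will be performed within three month of the inclusion of the last patient". The sentence names no endpoint. Under Objective of the study, evaluation and reporting of the clinical and laboratory results "will be done within three months after the end of recruitment"; that sentence then adds closure of the database as a further starting point, without dating it.

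**Visits.** In Trial population and patient recruitment (the text following the exclusion criteria), blood is drawn on postoperative day seven and at "follow-up/restaging visits (4 weeks postoperatively, four and seven months postoperatively"). The same paragraph adds: "Clinical examination will be performed and blood samples will be obtained by the investigators at all visits". For quality of life: "Quality of Life will be tested using the EORTC QLQ C-30 at four months and seven months postoperatively". Table 2 gives other times: "Quality of life according to EORTC QoL questionnaire after 3 and 6 months".

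**Endpoints that need follow-up.** The Objective section and Table 2 list local control, recurrence patterns, progression-free survival, overall survival and quality of life as secondary. The Follow up section sets imaging every three months.

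**Recruitment.** Objective of the study: "Usually, two patients per month can be enrolled into this study". It reports 35 patients randomised and four months to go. Statistical analysis sets the target at 40.

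**The concern.** Three months suits an endpoint measured on tissue removed at surgery. It does not suit endpoints observed up to seven months later. Surgery follows inclusion, so a patient included last cannot have a four- or seven-month visit within three months of inclusion. This needs no assumption. Using Table 2's times for quality of life does not remove the conflict, because month 6 is also too late.

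An analyst following the text must either break the stated date or report without planned time points for the most recent patients. Three things are at stake:

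- The seven-month blood and quality-of-life data would be incomplete in arms of about ten patients.
- The last patients would contribute at most one of the three-monthly imaging rounds to recurrence and progression.
- Statistical analysis names repeated measures ANOVA for continuous secondary endpoints such as plasma cytokines. If that were run on complete cases only, a missing last visit would remove the whole patient. The article does not say how incomplete visits are handled, so this consequence is conditional.

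The visits are scheduled anyway. Only the analysis date keeps them out.

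**Working it through.** **Inputs from the article**

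- Latest final analysis: T = 3 months after last inclusion (Study design).
- Last scheduled visit: v = 7 months after surgery (visit schedule). For quality of life, Table 2 gives v = 6, taken here as also counted from surgery.
- Number randomised: 40 (Statistical analysis).
- Recruitment rate: r = 2 per month as stated. A slower pace is implied if the four remaining months are read as recruitment time: (40 − 35)/4 = 1.25 per month.

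**Assumption.** The interval from inclusion to surgery, L, is not stated. I use 0 to 1 month.

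**The denominator.** Statistical analysis needs 32 analysable patients and allows 10–15% failure: 32/0.90 = 35.6, so 36; 32/0.85 = 37.6, so 38. The stated 40 is slightly above this and corresponds to 20% (32/0.80 = 40). I take 40 as given.

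**The recruitment statements.** At 2 per month the remaining 5 patients need 5/2 = 2.5 months, and four months at that rate would give 35 + 8 = 43. The two statements do not agree, so both paces are carried through.

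**Formula.** Count back from the last patient (k = 0), with inclusions evenly spaced at 1/r months. Patient k lacks visit v when v + L − k/r > T, that is, when k < r(v + L − T). The number missing is r(v + L − T), rounded up.

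**Results at the limit, T = 3**

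| Rate per month | Lag L (months) | Visit | r(v + L − T) | Missing of 40 |
|---|---|---|---|---|
| 2 | 0 | month 7 | 2 × 4 = 8 | 8 (20%) |
| 2 | 0.5 | month 7 | 2 × 4.5 = 9 | 9 (22.5%) |
| 2 | 1 | month 7 | 2 × 5 = 10 | 10 (25%) |
| 1.25 | 0 | month 7 | 1.25 × 4 = 5 | 5 (12.5%) |
| 1.25 | 1 | month 7 | 1.25 × 5 = 6.25 | 7 (17.5%) |
| 2 | 0 | month 6 (Table 2) | 2 × 3 = 6 | 6 (15%) |
| 2 | 0 | month 4 | 2 × 1 = 2 | 2 (5%) |
| 2 | 1 | month 4 | 2 × 2 = 4 | 4 (10%) |

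**Earlier in the window.** Three months is an upper limit. At 2 per month and no lag, the number lacking month 7 is 2 × (7 − 2) = 10 at T = 2, 2 × (7 − 1) = 12 at T = 1, and 2 × 7 = 14 (35%) at T = 0.

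**Delay needed for complete data.** 7 + L − 3 = 4 + L, so at least four months beyond the stated limit.

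**The case against.** **The database may close later.** The sentence under Objective of the study counts from the end of recruitment and also from database closure. Closure could follow the last follow-up visit, with reporting within three months of that. This stands: it would be wrong to say that both sections make the same mistake, or that the database closes before the late visits. But no closing date is given, nothing ties closure to the seven-month visit, and on the later reading the sentence conflicts with Study design. The two must be reconciled either way.

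**The data are not lost.** A reader might infer that the late data would never exist. The documents do not support that: the visits are scheduled regardless, and follow-up has no stated end. The data would be absent from the final analysis, and the article mentions no later one.

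**A fifth is one scenario.** A reader working only from the stated rate might settle on 8 of 40. The article's own remaining-time statement gives 5 of 40, so a range is the honest figure.

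**The damage is limited.** The confirmatory analysis uses resected tissue. The secondary analysis is described as descriptive. Blood taken before radiation, before surgery, on day seven and at four weeks is largely untouched. Survival has no fixed horizon here, so any cut-off censors late patients, and waiting to month 7 is not shown to be enough for survival. Missingness set by entry date is also unlikely to bias the randomised comparison. All of this stands, and it lowers the severity.

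**Cut-offs may be left to a fuller document.** That covers detail the article omits. It does not cover two dates the article states and that do not fit together.

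**Conclusion.** The conflict stands. An unqualified final analysis within three months of the last inclusion cannot contain the last patients' four- and seven-month visits. At the three-month limit, roughly 5 to 10 of 40 patients (12.5% to 25%) would lack month 7. This range rests on 40 randomised, even recruitment at 1.25 to 2 per month, and an assumed 0 to 1 month from inclusion to surgery. On Table 2's six-month time, quality of life would be missing for about 6 of 40 (15%) at 2 per month without lag.

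The primary tissue endpoint is not affected, and nothing here suggests biased arm comparisons. The harm is avoidable loss of information in the final report of secondary, mostly descriptive endpoints. The text should be corrected, but the primary conclusion does not depend on it.

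**What to change.** 1. In Study design, limit the analysis within three months of the last inclusion to the primary tissue endpoint.
2. Add a separate analysis of quality of life, serial blood and recurrence/survival, placed after the last patient's final scheduled visit, with a stated data cut-off.
3. Under Objective of the study, state that the database for these follow-up endpoints closes at that point.
4. Reconcile the quality-of-life times in the visit schedule (four and seven months) with those in Table 2 (3 and 6 months), so that the final scheduled visit is unambiguous.

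The cost is wording and a wait of at least four months for the secondary report (7 − 3 months, plus any time from inclusion to surgery). The primary result is not delayed.

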### Ethical and legal considerations

The final clinical trial protocol, the patient information and informed consent sheets were approved by the independent ethics committee of the University of Heidelberg S081/2008 (http://klinikum.uni-heidelberg.de). Furthermore, the study has been approved by the German Federal Authorities for Radiation Protection (Bundesamt fuer Strahlenschutz, Salzgitter, Trial Number Z5-22461/2-2009-002). Written informed consent is obtained from each patient in oral and written form before inclusion in the study. In addition, the protocol has been reviewed and funded by a scientific third party funding (grants from Nationales Centrum fuer Tumorerkrankungen (NCT)/Tumorzentrum Heidelberg and Kompetenzverbund Strahlenforschung (KVSF, 03NUK004A,C) of Bundesministerien fuer Bildung, Forschung und Umwelt (BMBF/BMU)). Patients are informed about the strict confidentiality of their personal data within this trial, but their pseudonymised medical records may be reviewed for trial purposes by authorized individuals other than their treating physician.

It has to be pointed out that the participation is voluntary and that the patient is allowed to refuse further participation in the protocol to any time point within the study. This trial is carried out in accordance to the current Declaration of Helsinki (sixth revision, 2008), the principles of "Good Clinical Practice" (GCP), and the Federal Data Protection Act. It is registered at the Clinical-Trials.gov protocol registration system (http://www.clinicaltrials.gov) and the assigned identification number is NCT01191632.

